# SAFE (Sarpogrelate Anplone in Femoro-popliteal artery intervention Efficacy) study: study protocol for a randomized controlled trial

**DOI:** 10.1186/s13063-017-2155-5

**Published:** 2017-09-22

**Keywords:** Endovascular treatment, Sarpogrelate, Peripheral artery disease, Stenosis, Femoro-popliteal

## Abstract

**Background:**

Sarpogrelate is expected to reduce restenosis by protecting blood vessels from oxidative stress and vascular endothelial dysfunction as well as by acting as an antiplatelet agent after endovascular treatment (EVT). This trial was designed to compare aspirin plus sustained-release (SR) sarpogrelate with aspirin plus clopidogrel for the prevention of restenosis in patients with femoro-popliteal (FP) peripheral artery disease (PAD) who underwent EVT.

**Methods/Design:**

This is an open label, multicenter, prospective randomized controlled clinical trial. Patients will be eligible for inclusion in this study if they require EVT for stenosis or occlusion of a de novo FP lesion. Patients in each group will receive aspirin 100 mg with clopidogrel 75 mg or aspirin 100 mg with SR sarpogrelate 300 mg (Anplone®) orally once a day for six months. The primary outcome of the study is the restenosis rate, defined as > 50% luminal reduction by computed tomography angiography or catheter angiography in the six-month follow-up period. Secondary outcomes include target lesion revascularization, major bleeding, ipsilateral major amputation, all-cause mortality, and all adverse events that take place in those six months.

**Discussion:**

This study is a multicenter randomized controlled trial designed to show non-inferiority in terms of the re-stenosis rate of SR sarpogrelate compared to clopidogrel for EVT for PAD in FP lesion patients.

**Trial registration:**

ClinicalTrials.gov, NCT02959606. Registered on 9 November 2016.

**Electronic supplementary material:**

The online version of this article (doi:10.1186/s13063-017-2155-5) contains supplementary material, which is available to authorized users.

## Background

After endovascular treatment (EVT) for peripheral artery disease (PAD), antiplatelet agents are used for three purposes: to prevent early thrombosis; to maintain long-term patency; and to reduce the incidence of cardiovascular events. Aspirin-based monotherapy or dual antiplatelet therapy (DAPT) are the most commonly used methods for these purposes [1]. Even though the common guidelines for PAD suggest mono-antiplatelet therapy, monotherapy alone may not be enough [2–5]. Surprisingly, however, there is no evidence-based recommendation for optimal antiplatelet therapy after EVT in PAD [6]. DAPT consisting of aspirin and clopidogrel, which is widely used, is only based on several cardiac-related studies [5].

However, even with the same antiplatelet agents, the effects may differ in cardiovascular disease (CAD) and PAD. For example, aspirin plus dipyridamol was effective in patients with CAD but not in those with PAD [7]. In addition, the incidence of not responding to clopidogrel was 30% higher in cases of EVT for PAD compared to percutaneous coronary intervention (PCI) [8]. Although the reasons for this phenomenon have not been uncovered, it may not be right to use the same DAPT in patients with PAD and CVD. Also, the role of antiplatelet therapy may be reduced or altered by technological developments in EVT. Therefore, an appropriate evidence-based recommendation of antiplatelet agents after EVT for PAD is needed.

Sarpogrelate is a selective 5-hydroxytryptamine receptor 2A antagonist that inhibits platelet aggregation, vasocontraction, and vascular smooth muscle proliferation [9]. Sarpogrelate is also expected to reduce restenosis by protecting blood vessels from oxidative stress and vascular endothelial dysfunction as well as by acting as an antiplatelet agent after EVT [10].

However, a commercially available immediate-release formulation of sarpogrelate (100 mg, three times per day) is not as convenient for patients to use as the currently used clopidogrel (75 mg, once daily). Fortunately, a sustained-release (SR) formulation of 300 mg sarpogrelate hydrochloride for once-daily usage has been introduced to improve convenience and compliance [11, 12].

This trial was designed to compare aspirin plus SR sarpogrelate with aspirin plus clopidogrel for the prevention of restenosis (>50% stenosis) at six-month follow-up in patients with femoro-popliteal (FP) PAD who underwent EVT.

## Methods/Design

### Study objectives, hypothesis, and design

This is an open label, multicenter, prospective randomized controlled clinical trial that will evaluate the efficacy and safety of aspirin plus SR sarpogrelate in PAD patients undergoing EVT for FP lesions compared with aspirin plus clopidogrel (ClinicalTrials.gov, NCT02959606). After baseline measurements and EVT, participants will be randomly allocated into the aspirin plus clopidogrel group or the aspirin plus SR sarpogrelate group. A brief flowchart of the whole study is presented in Figs. 1 and 2.

**Fig 1 Fig1:**
[figure not shown]
*Flow diagram* of SAFE study. *EVT* endovascular treatment, *ASA* aspirin, *R* randomization

**Fig. 2 Fig2:**
[figure not shown]
Standard Protocol Items: Recommendations for Interventional Trials (SPIRIT) figure (Additional file 1)

### Study population and eligibility

Patients will be eligible for inclusion in this study if they require EVT for stenosis or occlusion of a de novo FP lesion. To be eligible for randomization, patients must have adequate inflow and outflow (with or without intervention of the iliac or below-the-knee arteries) and successful FP intervention (residual stenosis < 30%). Previous intervention for an FP lesion is an exclusion criterion. Other inclusion and exclusion criteria are listed in Table 1.

**Table 1 Tab1:** Study eligibility criteria

*Inclusion criteria*	
Age > 18 years	
Angiographically confirmed significant FP stenosis or occlusion by atherosclerosis	
Successful FP intervention (residual stenosis < 30% after EVT)	
Without significant residual inflow disease; intact iliac artery inflow (with or without intervention of iliac or below knee arteries)	
Patent outflow status; at least one arterial runoff in BTK	
All kind of FP interventions including POBA, stent, DCB, DES for TASC A ~ D	
*Exclusion criteria*	
At risk of hemorrhage, bleeding tendency, or thrombophilia	
Acute limb ischemia / inflammatory arterial disease	
Contraindication or allergic to ASA, clopidogrel, Anplone	
Medication of warfarin	
Pregnancy, hepatic dysfunction, thrombocytopenia	
Previous FP bypass surgery or intervention	
Impossible to stop clopidogrel before EVT	
Unable to give informed consent.	

*FP* femoro-popliteal, *EVT* endovascular treatment, *BTK* below-the-knee, *POBA* plain old balloon angioplasty, *DCB* drug-coated balloon, *DES* drug-eluting stent, *TASC* The Trans-Atlantic Inter-Society Consensus, *ASA* aspirin

### Intervention and assessment schedule

All patients will be given a loading dose of 300 mg clopidogrel and 100 mg aspirin 24 hours or less before EVT. However, patients who have been treated with clopidogrel for > 5 days will receive 75 mg clopidogrel and 100 mg aspirin. Within 24 hours after successful FP intervention, the patients will be randomly assigned to the aspirin plus clopidogrel or aspirin plus SR sarpogrelate groups. Patients in each group will receive aspirin 100 mg with clopidogrel 75 mg or aspirin 100 mg with SR sarpogrelate 300 mg (Anplone®) orally once a day for six months.

### Follow-up

Outcomes will be recorded at 14 days and three and six months after intervention (Table 2). Information to be collected will include clinical and hemodynamic status, laboratory tests (complete blood cell count, liver function test, prothrombin time International Normalized Ratio), ankle–brachial index (ABI), adverse events, and other health problems and computed tomography angiography (CTA).

**Table 2 Tab2:** Assessment schedule

Visit date	Visit 1	Visit 2	Visit 3	Visit 4
	0 day	14 days	3 months	6 months
Demographic data	○			
Medical/surgical history	○			
Concomitant diseases	○		○	○
Concomitant medication/treatment	○		○	○
Physical examination (vital signs)	○	○	○	○
Laboratory results (CBC, LFT, PT INR)	○	○	○	○
ABI	○	○	○	○
CTA or angiography	○			○
Adverse events		○	○	○

*CBC* complete blood cell count, *LFT* liver function test, *PT* prothrombin time International Normalized Ratio, *ABI* ankle–brachial index, *CTA* computed tomography angiography

### Outcome measures

The primary outcome of the study is the restenosis rate, defined as > 50% luminal reduction by CTA or catheter angiography in the six-month follow-up period. Secondary outcomes include target lesion revascularization, major bleeding, ipsilateral major amputation, all-cause mortality, and all adverse events that take place in those six months.

### Adverse effects

Recording of serious adverse events (SAE) will conform to the Good Clinical Practice standards and the Research Governance Framework 2005. Analysis of safety-related data will be performed with respect to frequency of SAE including all-cause death, stroke, myocardial infarction (MI), or revascularization, early thrombosis, major bleeding, and major amputation. MI is defined as symptoms of ischemia with electrocardiographic changes compatible with MI or cardiac markers at least twice the upper normal limit [13]. Stroke is defined as brain hemorrhage, transient ischemic attack, or cerebral infarction with focal or global neurological deficits with signs or symptoms confirmed by a neurologist on the basis of neuroimaging results [14]. Major bleeding is defined as a need for a blood transfusion (≥ 2 packs), surgical intervention, or hypotension requiring inotropic support (hemoglobin reduction ≥ 2 g/dL). GUSTO bleeding criteria will be used [15]. Major amputation as a SAE is define as unplanned above-the-ankle amputation. Early thrombosis is defined as any event that occurs within 30 days after EVT. SAEs must be reported by the attending physician to the principal investigator within 24 h after the SAE becomes known.

### Statistical considerations

The aim of this study is to show the non-inferiority of sarpogrelate to clopidogrel in preventing restenosis. From the previous literature, we found a six-month restenosis rate in patients on clopidogrel of 11% and a six-month restenosis rate in patients on sarpogrelate of 6% following EVT for FP artery intervention (7). The targeted significance level is 2.5%; the sarpogrelate group proportion is assumed to be 16% under the null hypothesis of inferiority. A sample size of 136 in each group will achieve 80% power to detect a non-inferiority margin difference between the group proportions of 5% assuming a dropout rate of 10%.

Randomization will be done by an independent statistical core at the Medical Research Collaborating Center of Seoul National University Hospital. Permuted block randomization will be used with blocks of sizes 4 or 6 to ensure a balance between the two treatment groups. We will use SAS 9.4 (SAS institute Inc., Cary, NC, USA) for sequence generation, which is to be stratified for: (1) presence of occlusion within the index lesion; (2) use of stent; (3) TASC classification “A or B” vs. “C or D;” and (4) presence of critical limb ischemia. Allocation of treatment will be done via a web-based randomization system, which returns the treatment group after the input of a participant’s study ID and the inclusion/exclusion criteria.

Characteristics of participants will be summarized using mean and standard deviation for continuous variables and frequency and percentage for categorical variables. A two-sided 95% confidence interval for a difference in restenosis rate between the two treatment groups will be calculated; then, whether the upper limit of the confidence interval should fall within the pre-determined margin of non-inferiority will be evaluated to prove the non-inferiority of sarpogrelate to clopidogrel. The conclusion will be based on the result of intention-to-treat analysis, while the per-protocol analysis result will be provided by utilizing data on patients with treatment compliance > 80%. Among the secondary outcomes, adverse events will be analyzed using chi-squared tests or Fisher’s exact tests as appropriate. Major bleeding, ipsilateral amputation, revascularization, and all-cause mortality will be compared using log-rank tests and survival curves constructed using Kaplan–Meier methods.

Significance tests will be two-sided. A *P* value of < 0.05 according to SAS will be taken to indicate a statistically significant difference between the groups. SAS 9.4 (SAS institute Inc., Cary, NC, USA) will be used for data analysis.

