## Discussion

This study is designed to present evidence of the suitability of antiplatelet agents after endovascular revascularization in patients with FP arterial disease.

Some patients who participate in this study may have multi-level disease, including inflow or outflow problems as well as FP lesions, which may need to be corrected simultaneously. In other words, the inclusion criteria are broad, which reflects the situation in clinical practice. We will stratify the data on occlusion of the index lesion, use of stents, TASC AB and CD, and critical limb ischemia, which will help to determine the use of antiplatelet agent.

To date, DAPT, which consists of aspirin and clopidogrel, is well documented in patients with PCI. ESC guidelines recommend DAPT for one month after EVT with a stent for PAD [16]. However, the optimal antiplatelet agent is still unclear in long-term cases. The role of antiplatelet agents may decline after EVT for PAD owing to the development of new technology and devices that has occurred over the past decade [17]. Alternatively, the use of stronger antiplatelet agents may be required owing to various forces in the femoral artery during exercise and more aggressive treatment.

In the CAPRIE study, aspirin alone was associated with a higher rate of ischemic events than was clopidogrel [18]. That emphasized the necessity of DAPT rather than aspirin alone. Especially for cases of MI, ischemic stroke, and symptomatic PAD, DAPT with clopidogrel was more effective than ASA alone [19]. On the other hand, CASPAR failed to demonstrate a benefit of DAPT (aspirin plus clopidogrel), reminding us of the need for a variety of independent studies on the use of antiplatelet agents in PAD [20].

In one study, sarpogrelate reduced the restenosis rate (4.6% vs. 28.6%) after six months of coronary stenting [21]. There are three inhibitory effects of sarpogrelate: anti-platelet aggregation and anti-vasoconstriction prevent the development of early thrombus and anti-vascular smooth muscle proliferation is expected to reduce in-stent restenosis [9]. In addition, to protect endothelial cells by dose-dependently reducing the ICAM-1 level in a hyperglycemic state, it may also improve long-term patency after EVT [22].

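### Randomization is stratified on four factors but the primary confidence interval is described without them; if they predict restenosis, the interval is slightly too wide

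*Protocol article*

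**What the plan says.** All the relevant design text is in the protocol article, under Statistical considerations.

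- **Allocation.** "Permuted block randomization will be used with blocks of sizes 4 or 6", and the sequence is one "which is to be stratified for: (1) presence of occlusion within the index lesion; (2) use of stent; (3) TASC classification" (dichotomised, A or B against C or D), with critical limb ischemia as the fourth factor. Four binary factors make 2^4 = 16 strata.
- **Primary analysis.** "A two-sided 95% confidence interval for a difference in restenosis rate between the two treatment groups will be calculated". The upper limit is to be compared with the margin. No estimator, variance method or adjustment is named.
- **Sample size.** 136 per group, for 80% power at a 2.5% significance level, with rates of 11% (clopidogrel) and 6% (sarpogrelate), a margin of 5 points and 10% dropout.
- **Discussion section.** "We will stratify the data on occlusion of the index lesion, use of stents, TASC AB and CD, and critical limb ischemia". The sentence is not tied to the primary interval.

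**The concern.** Stratified allocation removes most of the chance imbalance between the arms on the stratifying factors. An unstratified standard error still charges for that imbalance. If the factors are related to restenosis, the standard error is then too large and the interval too wide.

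In a non-inferiority trial judged on the upper limit, a needlessly wide interval makes success harder. Planned power is 80%, so even a small gain in precision is worth having, and stratified allocation already requires the strata to be known for every patient.

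**Working it through.** **1. Reproduce the plan's sample size (unstratified formula).** Inputs from Statistical considerations: pC = 0.11, pT = 0.06, margin 0.05, one-sided alpha 0.025, power 0.80, dropout 10%.

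n = (1.960 + 0.842)² × [pC(1 − pC) + pT(1 − pT)] / (0.05 − (pT − pC))²

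= 7.849 × (0.0979 + 0.0564) / 0.10² = 121.1, so 122 per arm.

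122 / 0.9 = 135.6, so 136. This matches the plan exactly. The planning calculation makes no use of the strata.

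**2. Planned precision.** SE = √(0.1543 / 122) = 3.56 points; half-width 1.96 × 3.56 = 6.97 points.

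**3. Sparseness.** Expected events are 122 × 0.11 + 122 × 0.06 = 13.4 + 7.3 = 20.7. Over 16 strata that is about 1.3 events and 244 / 16 = 15 evaluable patients per stratum. A stratified method therefore needs a variance that holds in sparse tables.

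**4. Large-sample size of the effect.** With stratum shares w and stratum risks pCs and pTs:

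SE ratio (stratified / unstratified) = √{ Σ w [pCs(1 − pCs) + pTs(1 − pTs)] / [pC(1 − pC) + pT(1 − pT)] }

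Assumptions not in the documents: factor prevalences 50%, 60%, 50% and 30%, independent factors, and a common odds ratio (OR) per factor. The ratio is 1.000, 0.993, 0.981 and 0.952 at OR 1, 1.5, 2 and 3.

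**5. Simulation at the trial's size.** 16 strata and 11% against 6%. The unstratified Wald interval is compared with the Mantel-Haenszel (MH) difference. For stratum counts x1/m1 (sarpogrelate), x0/m0 (clopidogrel) and N = m1 + m0:

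- d = Σ[(x1·m0 − x0·m1)/N] / Σ[m1·m0/N]
- Sato variance = (d·P + Q) / (Σ[m1·m0/N])²
- P = Σ[m1²·x0 − m0²·x1 + m1·m0(m0 − m1)/2]/N²
- Q = Σ[x1(m0 − x0) + x0(m1 − x1)]/(2N)

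Three sets of simulated trials:

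- **A:** 6,000 per scenario, prevalences 50%, 50%, 50% and 30%.
- **B:** 2,500 per scenario, prevalences as in step 4, blocks of 4 or 6 within strata.
- **C:** 8,000 per scenario, 122 evaluable per arm on average.

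| OR per factor | Mean half-width, points (B) | Power, A | Power, B | Power, C |
|---|---|---|---|---|
| 1 | 6.93 → 6.95 | – | 80.1% → 80.1% | 81.4% → 80.9% |
| 1.5 | 6.92 → 6.91 | – | 82.7% → 82.6% | 82.0% → 82.1% |
| 2 | 6.91 → 6.81 | 81.4% → 82.5% | 81.7% → 82.8% | 82.4% → 83.0% |
| 3 | 6.94 → 6.66 | 81.8% → 84.0% | 82.8% → 85.0% | 81.7% → 84.2% |

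Arrows run from unstratified to stratified. The excess width of the unstratified interval is 6.91 / 6.81 − 1 = 1.5% at OR 2 and 6.94 / 6.66 − 1 = 4.2% at OR 3. The large-sample ratios of step 4 give 1.9% and 5.0%.

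**6. Type I error at the boundary (11% against 16%).** The unstratified interval wrongly declares non-inferiority in 2.2% to 2.7% of trials in set B, with Monte Carlo error √(0.025 × 0.975 / 2,500) = 0.3 points. Set A gave 2.0% at OR 3. The MH interval gave 2.1% to 3.0% in B and 2.4% to 3.0% in C. Both are close to the nominal 2.5%. The upper MH values suggest that it may be marginally liberal, so a little of the power gain could come from that.

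**The case against.** **The text is silent rather than wrong.** The article neither says that the interval is unadjusted nor excludes adjustment, and an analysis plan that is not shown may name a stratified estimator. That limits the point. Still, the article describes a plain two-group interval, names plain log-rank tests and sizes the trial with the unstratified formula, so the natural reading is an unstratified analysis.

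**The factors are not shown to be prognostic.** This stands. The article gives no rates by factor. OR 3 on all four factors at once means a 3^4 = 81-fold range of odds between extreme strata, which nothing in the article supports.

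**Nothing is at risk.** Also correct. An unstratified interval matches the sample-size calculation and delivers its planned 80%, and any error is conservative. A reader might infer that the primary test is invalid; the type I error results do not support that.

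**Stratifying is not free in sparse data.** Partly right: there are about 1.3 events per stratum, and occlusion and TASC class probably overlap, so some cells would be thinner than simulated. In set B, strata with patients in only one arm cost on average 0.1 of 244 patients.

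**Two further readings are tempting.** One is that the Discussion sentence plans to choose the drug by subgroup. It mentions no subgroup test and could equally mean stratified randomization, a stratified analysis or a descriptive split. The other is that the log-rank tests must be stratified too. With 16 cells and rare events such as death or amputation, that is debatable, because events in strata with only one arm at risk add nothing. Neither is part of this point.

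**Conclusion.** The point holds as a modest improvement to the primary analysis. As described, the primary interval does not use the strata within which patients are randomized. Across an assumed OR of 1 to 3 per factor, the simulated change in power from stratifying runs from −0.5 points (no prognostic value) to +2.5 points (OR 3); at OR 2 it is 0.6 to 1.1 points. These figures also rest on assumed prevalences, independent factors and 122 evaluable patients per arm.

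The documents do not support a stronger statement: the prognostic strength of the factors is unknown, and a non-inferiority claim based on the unstratified interval would remain sound.

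**What to change.** State in the analysis plan, before outcome data are examined by arm:

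- The primary estimate is the Mantel-Haenszel risk difference (sarpogrelate minus clopidogrel) over the randomization strata, with the Sato variance and a two-sided 95% confidence interval. Its upper limit is compared with the 5-point margin.
- Strata are taken as recorded at randomization, and the plan says how a stratum with patients in only one arm is handled.
- The unstratified interval is reported as a sensitivity analysis.

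The cost is a short paragraph and a few lines of SAS, with no new data and no change to the sample size. The price is a slightly less simple primary estimate and, if the factors do not predict restenosis, essentially no gain or a very slight loss (half-width 6.93 to 6.95 points in the simulation).

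### The non-inferiority conclusion rests on intention-to-treat alone; the per-protocol result need not agree, so dilution between the arms can make the claim easier at the margin

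*Protocol article*

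**What the plan says.** All of the following is in the protocol article.

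- **Aim** (Statistical considerations): "The aim of this study is to show the non-inferiority of sarpogrelate to clopidogrel in preventing restenosis".
- **Blinding** (Study objectives, hypothesis, and design): "This is an open label, multicenter, prospective randomized controlled clinical trial that will evaluate the efficacy and safety".
- **Test** (Statistical considerations): a two-sided 95% confidence interval for the difference in restenosis rates, with its upper limit compared with a 5-point margin. On the error rate and the null: "The targeted significance level is 2.5%; the sarpogrelate group proportion is assumed to be 16% under the null hypothesis of inferiority". The clopidogrel rate is taken as 11%.
- **Which analysis decides** (same section): "The conclusion will be based on the result of intention-to-treat analysis, while the per-protocol analysis result will be provided".
- **Per-protocol set** (same section): formed by "utilizing data on patients with treatment compliance > 80" per cent. No other criterion is given. The sentence does not name the drug to which compliance refers, or say how use of the other arm's drug is treated.
- **Data on other drugs** (Follow-up, Table 2): the row "Concomitant medication/treatment" is marked at day 0, three months and six months.

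**The concern.** In a superiority trial, contamination between arms usually works against the claim. In a non-inferiority trial it can work for it. If sarpogrelate is truly worse, every sarpogrelate patient who moves to clopidogrel, and every clopidogrel patient who moves to sarpogrelate, brings the two ITT rates closer and makes the margin easier to meet. ITT and per-protocol results are usually read together for this reason.

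Here the article fixes the rule itself: ITT decides and per-protocol is reported beside it. Contamination is plausible. Treatment is known to patient and physician, every patient receives clopidogrel before the procedure (Intervention and assessment schedule), and the Background describes aspirin plus clopidogrel as widely used. At stake is a claim of non-inferiority that arises partly because patients did not stay on the assigned regimen, with no part of the decision rule able to stop it.

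**Working it through.** **Inputs.** From Statistical considerations: clopidogrel 11%; sarpogrelate 6% under the design alternative and 16% under the null; margin 5 points; one-sided 2.5% (the upper limit of a two-sided 95% interval); power 80%; dropout 10%; 136 per group. Assumed, because the document gives neither: the amount of dilution (0% to 30%) and the share of patients who comply (80% to 95%).

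**Step 1: reproduce the plan's sample size.** With unpooled variance,

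n = (1.96 + 0.842)² × [0.11×0.89 + 0.06×0.94] / (0.05 + 0.05)² = 121.1, rounded up to 122 evaluable per group.

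122 / 0.90 = 135.6, rounded up to 136. This matches the plan, so the checks below use 122 per arm and the same test.

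**Step 2: false non-inferiority rate under dilution.** Let a share q of sarpogrelate patients have the clopidogrel rate because they take clopidogrel. Then

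- ITT difference d = 0.05 × (1 − q)
- SE = √{[0.11×0.89 + (0.11+d)(0.89−d)] / 122}
- false non-inferiority rate = Φ[(0.05 − d)/SE − 1.96]

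| q | d | SE | (0.05 − d)/SE | Rate | Exact binomial |
|---|---|---|---|---|---|
| 0 | 0.050 | 0.0436 | 0 | 2.5% | 2.8% |
| 10% | 0.045 | 0.0433 | 0.115 | 3.3% | 3.6% |
| 20% | 0.040 | 0.0430 | 0.233 | 4.2% | 4.6% |
| 30% | 0.035 | 0.0426 | 0.352 | 5.4% | 5.9% |

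The exact column enumerates all outcomes under the same interval rule. It shows the same rise, so the pattern does not come from the normal approximation. If the same share switches in both directions, the rate by the formula is 4.2% at 10%, 6.7% at 20% and 10.1% at 30%.

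**Step 3: the other direction.** At 6% versus 11%, one-way switching moves the sarpogrelate rate up to 0.06 + 0.05q. The probability of passing falls from 80.3% to 75.0% at q = 10% and 69.2% at q = 20%. Dilution then works against the claim.

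**Step 4: cost of requiring both sets to pass.** I took 6% versus 11%, 122 evaluable per arm, and a compliant subset with the same event rates as the rest of its arm. Power for the per-protocol set alone is Φ[0.10/SE − 1.96]. The joint figure comes from simulating binomial counts with the per-protocol patients nested within ITT; on that basis ITT alone passes in 81.8%.

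| Compliant | Per-protocol n per arm | Per-protocol alone (formula) | Both pass (simulated) |
|---|---|---|---|
| 95% | 115 | 78% | 78% |
| 90% | 109 | 76% | 75% |
| 80% | 97 | 71% | 70% |

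To keep 122 compliant evaluable patients at 90% compliance: 122/0.9 rounds up to 136, and 136/0.9 rounds up to 152 per group.

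**The case against.** The best defence is that ITT preserves randomization, whereas a set selected on compliance after randomization can be biased in either direction. Both results will be reported, so disagreement would be visible. That is a sound reason not to let per-protocol decide alone. It does not answer the point, because under the stated rule a visible disagreement still leaves the conclusion unchanged.

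Two further objections stand and limit the point. The inflation arises only if sarpogrelate is truly worse by about the margin, whereas the design assumes it is better; open-label treatment makes switching more likely but does not itself create the bias. And the model in Step 2 describes patients who take on the other arm's rate. A sarpogrelate patient who simply stops does not acquire clopidogrel's rate, so plain non-adherence need not shrink the difference. At 10% one-way dilution the excess is only 0.8 points.

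A reader might also infer more than the text supports:

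- *That the per-protocol set keeps patients who crossed over.* The article does not say so. Compliance reads naturally as compliance with the assigned drug, so an early switcher falls below 80% and leaves the set. Only someone who adds the other drug while taking more than 80% of their own, or who switches in roughly the last fifth of the six months, could remain.
- *That the 80% rule has no data behind it, because Table 2 shows no pill count and no concomitant-medication mark at Visit 2.* A condensed article commonly leaves drug accountability to the full protocol, which is not shown. Table 2 does schedule concomitant medication at three visits.

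**Conclusion.** The point holds in a conditional form. ITT alone decides a non-inferiority claim in an open-label trial, and nothing requires the per-protocol result to agree. Because the article states this as its rule, it is not a detail left to a fuller document. At the margin (16% versus 11%, 122 per arm), one-way dilution of 10%, 20% or 30% gives a false non-inferiority rate of 3.3%, 4.2% or 5.4% instead of 2.5%. These figures rest on assumed dilution and on switchers taking the other arm's rate; the true cross-over rate is unknown. The plan should change the rule, but ITT is not shown to be anti-conservative in every case, and no flaw in data collection is shown.

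**What to change.** Change the decision rule in Statistical considerations: non-inferiority is claimed only if the upper limit of the two-sided 95% confidence interval lies below 5 points in both the ITT and the per-protocol set. Define per-protocol as more than 80% compliance with the assigned agent and no sustained use of the other arm's study drug after randomization, with the length that counts as sustained fixed before any outcome data are seen. This defines an analysis set only and does not change how patients are treated.

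The wording is cheap to change while recruitment is ongoing, as the Trial status section reports. The real cost is power. The chance of passing both sets is about 78%, 75% or 70% at 95%, 90% or 80% compliance, so the stated 80% should be restated with the compliance it assumes. If the sponsor prefers to keep 122 compliant evaluable patients per group, 90% compliance requires about 152 per group instead of 136. That restores the per-protocol set's own power; the joint probability would still be slightly lower than the per-protocol figure.
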